## Abstract

**Background:**

Previous studies have shown that patients’ anxiety and dissatisfaction are predictors for increased postoperative pain and reduced efficacy of pain treatment. However, it remains to be shown whether patient anxiety and concern are predictors for the perceived quality of treatment and patient reported outcome (PRO).

The aim of this study is to investigate whether there is a correlation between preoperative anxiety and concern, and the perceived quality of postoperative treatment and outcome. The hypothesis is that anxious and concerned patients are less satisfied with treatment and have a poorer outcome.

**Methods/design:**

This study is designed as a prospective follow-up study and has the aim of investigating the correlation between patient anxiety and concern, patients´ perceived quality of treatment and outcome. This correlation will be detected using five questionnaires: CMD-SQ (Common Mental Disorders Screening Questionnaire), EuroQol 5 Dimensions (EQ-5D), Short form 12 (SF-12), “What is your evaluation of the patient progress in the Department of Orthopaedic Surgery?” (HVOK), Questionnaire for patients who have had hip surgery (RCS) and Oxford Hip Score (OHS) or Oxford Shoulder Score (OSS). The patients will complete the above mentioned questionnaires preoperatively in the outpatient department, and postoperatively just before discharge from the inpatient department, and 12 and 52 weeks after the operation. The study includes a reliability test of CMD-SQ regarding this specific population and tested by means of a Kappa. A total of 500 hip- and shoulder-patients will be included from October 2010 till October 2011.

**Discussion:**

If a correlation between patient anxiety and concern, patients´ perceived quality of treatment and patient reported outcome is found, it will be recommended to screen all hip- and shoulder-patients for anxiety and concern preoperatively. Besides, it would be relevant to carry out investigations of possible interventions towards anxious and concerned patients.

**Trial registration:**

Current Controlled Trials: NCT01205295

## Background

Studies of patients´ reported quality of treatment has shown in general, that patients are very satisfied with their treatment
[1-3]. However, studies investigating the correlation between patients´ satisfaction with treatment and their perceived outcome are warranted.

The overall aim of orthopaedic treatment is to reduce pain, improve functional ability and thereby enhance quality of life
[4]. A study based on the Oxford Hip Score (OHS) showed a significant correlation between the clinical outcome measured by OHS, patients´ perceived quality of life (EQ-5D), and their satisfaction with treatment
[5] following insertion of a total hip arthroplasty (THA). In addition, a Swedish study showed that preoperative depression and anxiety (detected by EQ-5D) had a significant correlation with postoperative satisfaction and pain as regards THA patients
[6]. The patients, who were most dissatisfied with the treatment and suffered from anxiety or depression, had the smallest pain relief. However, the study underscored the need for future research by means of a more specific and sensitive questionnaire for detecting anxiety and depression preoperatively, as the study was a prospective registry trial, without opportunity for further data collection. Thus, it would be relevant to conduct a study using a more sensitive questionnaire to detect anxiety, depression and concern and their influence on postoperative patient reported outcome (PRO).

Another studies have shown a correlation between dissatisfaction with therapy, and moderate to severe postoperative pain
[7,8]. Studies have shown a significant correlation between anxiety, mood and chronic pain
[9,10], and that patients are 2–3 times more likely to develop chronic pain if they already suffer from a kind of depression
[11,12].

A Danish study conducted by general practitioners showed a significant correlation between patients' somatoform disorder and their satisfaction with treatment
[13]. Another study based on the Common Mental Disorders (CMD-SQ) questionnaire showed that it is possible to identify anxious and concerned patients and then focus on their treatment
[14].

Some studies have revealed that far from all patients get the relief they are searching for by traditional therapies such as surgery and medical treatment
[15,16], and that there are patients who do not receive the warranted treatment in health services
[17,18]. If it is possible to identify these patients, a more targeted treatment could be used in a combination with the traditional treatment.

However, it remains to be shown whether patient anxiety and concern are predictor factors for the perceived quality of treatment and the patient reported outcome. This project is expected to reveal more precise information on the correlation between patient anxiety and concern and patients reported outcome (PRO) than previous studies have shown.

### Aim and hypothesis

The aim of this study is to investigate whether there is a correlation between patient anxiety and concern, and patients´ perceived quality and outcome of treatment. The hypothesis is that patients who are anxious and concerned are less satisfied with their treatment and have a poorer outcome.

### Material

#### Conceptual clarifications

Anxiety is an unpleasant state of mind which reduces the individuals’ ability to function in daily life. Anxiety can vary in different modes of expression, such as: agoraphobia, social phobia, simple phobia, panic disorder, generalized anxiety, obsessive-compulsive disorder, acute stress disorder and post-traumatic stress disorder
[19].

Concern is defined as thoughts about things or events that may occur in life which can be positive or negative. These thoughts cause restlessness and a fear of harming one's own health and may reduce patients´ control and disable them
[20]. In this study anxiety and concern are detected by the Common Mental Disorders - Screening Questionnaire (CMD-SQ) and EQ-5D.

CMD-SQ (Common Mental Disorders – Screening Questionnaire) contains 38 items and was prepared as a tool for general practitioners to increase the focus on patients` anxiety and concern. The questionnaire was translated into Danish and then validated without the test-retest. The validation tests included a total of 701 patients and the results of the CMD-SQ were compared to the SCAN-interview which was used as a golden standard. The analysis showed a Kappa of 0.86
[14,21,22]. CMD-SQ consists of the following six subscales, each of them has been validated: SCL-SOM, Whiteley-7, SCL-ANX4, SCL-8, SCL-DEF6 and CAGE
[14]. The patients respond on at five point Likert scale. A normal sum score is lower than four in the SCL-AS scale and no more than two in the remaining scales based on the cut points on the ROC curve. A manual for assessing and validating the score of CMD-SQ is available
[14].

EQ-5D (EuroQol 5 Dimensions) is designed to assess the health related quality of life with no reference to a specific diagnosis. The questionnaire has been translated into Danish and validated
[23]. The scale includes five broad areas and a visual analogue scale. The self-reported health situation is reported on a scale from 0 to 100. The score 100 corresponds to the best self-reported health situation
[24].

The perceived quality is the patients´ satisfaction with treatment detected by the questionnaire HVOK, including patients admitted to the Department of Orthopaedic Surgery. HVOK is the Danish acronym for the title which translated into English is “What is your evaluation of the patient progress in the Department of Orthopaedic Surgery?”

The Danish questionnaire HVOK includes 46 items and deals with patients' priorities and satisfaction with treatment and is included in a revised form. The questionnaire has been pilot tested at 38 patients
[25]. Ten of the highest prioritised items were selected for this study. The patients respond on at five point Likert scale.

The Royal College of Surgeons of England has developed the "Questionnaire for patients who have had hip surgery" (RCS). The aim was to investigate patients´ satisfaction with surgery
[26]. It is relevant to include three items as supplementary questions in this study. The patients respond on at a five point Likert scale. This three items are 1) “In general, would you say your health is?”, 2) “How will you describe the result of your operation?” and 3) “Overall, how are the problems now in the hip on which you had surgery, compared to before your operation?”

Patient reported outcome (PRO) is defined as the patients outcome of the treatment measured by SF-12 (Short Form 12) and OHS (Oxford Hip Score) or OSS (Oxford Shoulder Score)
[27].

The UK questionnaires OHS and OSS are similar, but related to two different categories of patients, namely THA (Total Hip Arthoplasty) and shoulder-operated patients. The questionnaires are compiled and validated in Oxford University Hospital. Each questionnaire contains 12 items and both scores have been translated into Danish
[28]. The OSS has been translated into Danish and validated
[29]. The patients respond on at five point Likert scale and the sum scores can be between 12 and 60 points. 12 points reflects the best possible outcome, and a score above 36 is categorized as an expression of a poor patient-assessed outcome
[27].

SF-12 is an internationally and nationally validated questionnaire that evaluates patients' self-reported health perception. SF-12 is an abbreviated version of SF-36 and it contains 12 items, which are divided into physical and mental items. The patients respond on a Likert scale
[30-32].

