### Statistical analysis

The test-retest reliability is analyzed by means of an Kappa and a value above 0.70 is recommended in a clinical study
[42].

The data from the preoperative questionnaire, the postoperative questionnaire just before discharge from the inpatient ward, and the questionnaire data from 12 and 52 weeks after the operation, will be analysed using a multiple linear regression test in order to investigate whether there is a correlation between patients´ anxiety and concern, and their perceived quality and outcome of treatment. It is assumed that the data are normally distributed and the will be made to different Multiple Linear Regression analysis where the first will be between baseline and after 12 weeks and the second between baseline and 52 weeks.

The results of the CMD-SQ before the operation and 3 and 12 months postoperatively, are considered the primary outcome, whereas the results of SF-12, EQ-5D, OHS/OSS, RCS and HVOK are the secondary outcome. The main result is a correlation between the primary outcome and the secondary outcomes. The analysis will be done separately and without mutual influence.

Data will be tested for confounder using the Charlson Index and social demographic data (i.e.: gender, age, weight, height, citizenship, civil status and educational level).

Missing data will be labelled as missing in all the questionnaires. For the comparative analysis for the dropouts and the respondents the categorical variables as gender, citizenship, civil status, Charlson Index and educational level will be analyzed using a chi^2 test. For the continuous variables age, weight and height will be analyzed by using a t-test. Potentially dropouts after the first measurement will be analysed with respect to the social demographic data and compared to those of the patients who stay in the study. All dropout analysis will be done by means of an unpaired t-test.

All statistical analyses are done using Stata, version 11.

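### EQ-5D is named both as a detector of anxiety and as an outcome, and CMD-SQ shares mood content with EQ-5D and the SF-12 mental items

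*Protocol article*

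**What the plan says.** All places are in the protocol article.

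- **Exposure.** *Conceptual clarifications*: "In this study anxiety and concern are detected by the Common Mental Disorders - Screening Questionnaire (CMD-SQ) and EQ-5D".
- **Outcomes.** *Statistical analysis* makes CMD-SQ, before and after operation, the primary outcome, "whereas the results of SF-12, EQ-5D, OHS/OSS, RCS and HVOK are the secondary outcome". It continues: "The main result is a correlation between the primary outcome and the secondary outcomes".
- **Definition of patient-reported outcome (PRO).** *Conceptual clarifications* says that PRO is "measured by SF-12 (Short Form 12) and OHS (Oxford Hip Score) or OSS (Oxford Shoulder Score". EQ-5D is not in that definition. Perceived quality is assigned to HVOK.
- **Content of EQ-5D.** The same section says that it "is designed to assess the health related quality of life with no reference to a specific diagnosis", and: "The scale includes five broad areas and a visual analogue scale". *Background* cites an earlier study of "preoperative depression and anxiety (detected by EQ-5D", so the authors themselves treat EQ-5D as carrying mood information.
- **Content of SF-12.** "it contains 12 items, which are divided into physical and mental items".
- **Content of CMD-SQ.** Six subscales. The *Abbreviations* list describes them as somatisation, illness worry, anxiety, mental illness, depression and alcohol dependence.

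**The concern.** There are two linked problems.

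First, one instrument is placed on both sides of the association under test. EQ-5D helps to define who is anxious, and it is also one of the results that anxious patients are expected to do worse on. The PRO definition, which omits it, adds a third account of its role.

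Second, removing EQ-5D from the exposure does not remove the overlap. CMD-SQ asks about anxiety, depression and mental illness. EQ-5D and SF-12 partly ask about the same state. A patient who is anxious before surgery and still anxious a year later scores badly on both sides, however well the joint has done.

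At stake is the reading of the hypothesis that anxious patients have a poorer outcome. A correlation with EQ-5D or with the SF-12 mental items could be taken as support for it when it shows only that low mood persists.

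**Working it through.** **Step 1: the passages side by side**

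| Instrument | Role in the definitions | Role in the analysis | Mood content shown in the article |
|---|---|---|---|
| CMD-SQ | Detects anxiety and concern | Variable correlated with all others | Yes: anxiety, depression, mental illness |
| EQ-5D | Detects anxiety and concern; not in PRO | Secondary outcome | Yes (*Background*) |
| SF-12 | PRO | Secondary outcome | Yes: mental items |
| OHS/OSS | PRO | Secondary outcome | None described |
| HVOK | Perceived quality | Secondary outcome | None described |
| RCS, operation result and hip problems | Supplementary | Secondary outcome | None in the wording |

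EQ-5D has conflicting roles. EQ-5D and SF-12 both share content with CMD-SQ. *Statistical analysis* promises separate analyses, but this separates one outcome from another; it does not separate the items within an instrument. The listed confounders (Charlson Index and sociodemographic data) do not deal with it either.

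**Step 2: an illustration of size**

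The article gives no figure to reproduce: no inter-item correlations, no EQ-5D scoring rule and no number of mental items in SF-12. The following inputs are assumptions, except the 202, which *Discussion* calls the required sample size.

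- EQ-5D is scored as a sum of five equally weighted items with unit variance.
- One item correlates c = 0.4, 0.6 or 0.8 with CMD-SQ. The other four have no correlation with it.
- The four non-mood items correlate 0.3 with each other.
- The mood item correlates with those four either 0 (case A) or 0.3 (case B).

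Induced correlation: r = c / √Var, where Var is the variance of the sum.

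- Case A: Var = 4 + 12 × 0.3 + 1 = 8.6, √Var = 2.933.
- Case B: Var = 5 + 20 × 0.3 = 11, √Var = 3.317.

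| c | Case A | Case B |
|---|---|---|
| 0.4 | 0.136 | 0.121 |
| 0.6 | 0.205 | 0.181 |
| 0.8 | 0.273 | 0.241 |

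Detectable correlation by Fisher's z, two-sided 5% and 80% power (both assumed): tanh((1.960 + 0.842) / √(n − 3)). With n = 202 this is tanh(2.802 / 14.107) = 0.196. With n = 250 it is 0.176.

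The middle row lies above 0.196 in case A and below it in case B. Whether overlap alone reaches the detectable value thus depends on an inter-item correlation that the article does not give.

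**Step 3: SF-12, same method**

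For a 12-item sum in which m items overlap and all items correlate 0.3 with each other, r = m × c / √(12 + 132 × 0.3) = m × c / 7.183.

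- m = 3, c = 0.2 to 0.5: 0.08 to 0.21.
- m = 6, c = 0.2 to 0.3: 0.17 to 0.25.

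The item counts and correlations are again assumptions.

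**The case against.** The strongest reply is that the working exposure is CMD-SQ alone. *Statistical analysis* puts only CMD-SQ on the anxiety side, and *Discussion* identifies anxious and concerned patients by a high CMD-SQ score. This stands. A reader might infer that EQ-5D will be correlated with itself, but no planned analysis uses it as a predictor. What remains of the double role is a contradictory definition, together with the content shared with CMD-SQ.

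A reader might also infer that overlap alone could trigger the recommendation to screen all patients. The documents do not support that. The *Abstract* ties the recommendation to a correlation that involves perceived quality as well as PRO, and the hypothesis in *Discussion* also covers satisfaction. HVOK, with no mood content described, would have to correlate too.

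Three further replies carry some weight.

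- *Scoring.* The only EQ-5D score that the article describes is the 0 to 100 self-rating. If only that is analysed, the five-item illustration does not apply. The choice of score may be settled in a document not shown.
- *Timing.* Outcomes at 12 and 52 weeks should correlate less with preoperative CMD-SQ than same-day scores would. This weakens the overlap but does not remove it where mood persists. The article also counts postoperative CMD-SQ as primary outcome, so same-time correlations are not excluded.
- *Legitimacy.* *Background* makes quality of life an aim of orthopaedic treatment, so mental quality of life is a fair outcome to report. That argues for keeping these scores, with the overlap stated, rather than dropping them.

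**Conclusion.** The point holds in a limited form. The article contradicts itself on the role of EQ-5D. Separately, CMD-SQ shares mood content with EQ-5D and with the SF-12 mental items, so part of a correlation with these scores may reflect persistent mood rather than the result of surgery.

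The size cannot be derived from the documents. Under the EQ-5D assumptions above, the induced correlation is about 0.12 to 0.27, which straddles the 0.20 or so detectable with 202 patients. It would be wrong to say that overlap alone is bound to produce a detectable result; it could do so in part of the range. The contradiction and the shared content follow from the text and do not depend on these figures.

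OHS/OSS, HVOK and the RCS items on operation result and hip problems are untouched on this ground, so the study keeps outcomes on which the hypothesis can be tested.

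**What to change.** 1. In *Conceptual clarifications*, delete EQ-5D from the detection of anxiety and concern, and name CMD-SQ as the only exposure.
2. Base the conclusion on poorer outcome on OHS/OSS and the SF-12 physical score.
3. Keep EQ-5D and the SF-12 mental score as secondary outcomes, reported separately. Show EQ-5D with and without its anxiety/depression dimension, and state that these scores overlap with the exposure.

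The cost is in wording, scoring and reporting; no extra patient, visit or questionnaire is needed. The small downside is that the full EQ-5D index and the SF-12 mental score no longer count, on their own, as support for the hypothesis. That modestly changes what the stated outcomes can show.

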## Methods

### Design

The study is designed as a prospective follow up study. The patients will complete the questionnaires, once preoperatively in the outpatient department and three times postoperatively; before discharge and 12 and 52 weeks after the operation. The inclusion period will be one year beginning in October 2010. The study includes a reliability test of CMD-SQ regarding this specific population, and investigated by means of a Kappa.

The reliability of CMD-SQ is tested by including 40 patients who will answer the CMD-SQ two times. The aim is to investigate whether the questionnaire responses will change over time regarding this specific population (test-retest). The hip patients will be asked to fill in the CMD-SQ at first in the outpatient department, when they join the Joint Care School, and next when they arrive to the inpatient department just before their operation. The main issue is that no essential changes had happened to the patients between the two measurements.

After the test-retest of the CMD-SQ, patients will be included for the next part of the study. When the hip patients arrive to the Joint Care School, they are asked to fill in the questionnaires: CMD-SQ, EQ–5D, SF–12, RCS and OHS. The shoulder patients are asked to fill in the questionnaires: CMD-SQ, EQ-5D, SF-12 and OSS when they arrive to the outpatient department for the first time. Both groups – hip and shoulder patients will be asked to fill in the questionnaire HVOK just before their discharge from the inpatient department. The patients are asked to fill in the questionnaires: CMD-SQ, EQ-5D, SF-12, RCS, HVOK and OHS/OSS 12 and 52 weeks after the operation. Postoperatively, the questionnaires are sent to the patients by mail and the patients are asked to return the questionnaire in the enclosed stamped and addressed envelope. If the patients do not return the questionnaire in 14 days, a new questionnaire is mailed. If the second questionnaire is not returned the patients are called and asked to return the questionnaire, or asked why they do not want to fill in the questionnaire. These precautions are taken in order to increase the response rate.

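### As printed, two of the three RCS items do not fit some of the patients and visits they are assigned to, and discharge HVOK belongs to neither named regression

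*Protocol article*

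**What the plan says.** Conceptual clarifications selects three RCS items as supplementary questions, from an instrument titled for people who have already had hip surgery. Item 1 is about general health ("In general, would you say your health is"). Item 2 asks the patient to describe how the operation turned out. Item 3 is "Overall, how are the problems now in the hip on which you had surgery, compared to before your operation".

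Design sets the schedule by joint and visit:

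- Before surgery, hip patients at the Joint Care School: "they are asked to fill in the questionnaires: CMD-SQ, EQ–5D, SF–12, RCS and OHS".
- Before surgery, shoulder patients, with no RCS in the list: "The shoulder patients are asked to fill in the questionnaires: CMD-SQ, EQ-5D, SF-12 and OSS when they arrive to the outpatient department".
- At discharge, both groups: HVOK.
- At follow-up, both groups: "The patients are asked to fill in the questionnaires: CMD-SQ, EQ-5D, SF-12, RCS, HVOK and OHS/OSS 12 and 52 weeks after the operation".

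The abstract's Methods/design paragraph is looser. It lists all the instruments, HVOK and RCS included, and then says: "The patients will complete the above mentioned questionnaires preoperatively in the outpatient department".

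Conceptual clarifications defines perceived quality as satisfaction measured by HVOK. Statistical analysis first names the preoperative, discharge, 12-week and 52-week questionnaires as the data for multiple linear regression. It then describes two regressions: "the first will be between baseline and after 12 weeks and the second between baseline and 52 weeks". It lists RCS and HVOK among the secondary outcomes, and calls the correlation of the primary outcome (CMD-SQ) with the secondary outcomes the main result.

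**The concern.** There are two separate problems.

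The first is a mismatch between item wording and schedule. A hip patient at the Joint Care School is still waiting for the operation that items 2 and 3 ask about, so any answer recorded there has no meaning. A shoulder patient at follow-up has no operated hip. Some will leave item 3 blank, some will answer about the shoulder, and some may answer about a hip. The analyst could not tell the last two apart.

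The second is an analysis gap. HVOK carries the perceived-quality part of the hypothesis, and discharge is the occasion closest to the treatment being judged. If no model is named for it, whether and how it is reported can be decided after the data have been seen.

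**Working it through.** No figure in the plan is in dispute, so the check sets the sections side by side and counts.

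**Step 1. Is the Joint Care School visit before surgery?** Yes. Design opens with one preoperative completion in the outpatient department. Its test-retest paragraph places the first CMD-SQ at the Joint Care School and the second on arrival at the ward, before the operation.

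**Step 2. Do the RCS items fit each group and visit?** Items are from Conceptual clarifications, visits from Design.

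| RCS item | Hip, before surgery | Hip, 12 and 52 weeks | Shoulder, before surgery | Shoulder, 12 and 52 weeks |
|---|---|---|---|---|
| 1, general health | fits | fits | not given | fits |
| 2, result of the operation | does not fit | fits | not given | fits |
| 3, the hip now against before | does not fit | fits | not given | does not fit |

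Item-by-visit combinations:

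- Hip, before surgery: 3 items × 1 visit = 3, of which 2 do not fit.
- Hip, follow-up: 3 × 2 = 6, of which 0 do not fit.
- Shoulder, follow-up: 3 × 2 = 6, of which 2 do not fit (item 3, twice).
- Total: 4 of 15.

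With the planned 250 patients per joint (Sample size section) and complete response, that is at most 250 × 2 = 500 hip answers and 250 × 1 × 2 = 500 shoulder answers.

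**Step 3. Is a shoulder version stated?** The follow-up list writes OHS/OSS, so it covers shoulder patients and marks a joint-specific version where one exists. RCS carries no such mark, and no adapted wording of item 3 is given.

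**Step 4. Which HVOK occasions have a model?**

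| HVOK occasion (Design) | Among the data for regression? | In a named regression? |
|---|---|---|
| Discharge | yes | no |
| 12 weeks | yes | yes, baseline to 12 weeks |
| 52 weeks | yes | yes, baseline to 52 weeks |

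One of three occasions is promised for regression but has no named model.

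**Step 5. Abstract against Design.** Read literally, the abstract has HVOK completed before surgery by everyone and RCS before surgery by shoulder patients. Design has neither.

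**The case against.** The strongest case on the other side has four parts.

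- **A reader might infer that discharge HVOK is collected and never analysed, or taken at the wrong time.** Neither is supported. Statistical analysis explicitly includes the discharge questionnaire in the data for regression, and discharge is a sensible time to ask about satisfaction. What stands is an inconsistency between two neighbouring sentences: the data are promised, and the models then named do not use them.
- **A reader might infer that RCS lacks a valid baseline and its follow-up analysis therefore fails.** This does not follow. Items 2 and 3 are retrospective and need no baseline value. Follow-up RCS can be related to preoperative CMD-SQ directly, and the plan states no analysis of change in RCS. What stands is that RCS is on the hip preoperative list with no restriction to item 1.
- **A reader might infer that item 3 is unusable in shoulder patients.** That goes beyond the text. The items are printed in English, the patients must read Danish, and the forms used are not shown; an adapted shoulder form may exist. What stands is that the article prints hip wording, gives RCS to both joints and states no adaptation.
- **The abstract is only compressed.** This is fair. Design gives the operative schedule, so that mismatch is editorial.

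The weight of the RCS items is also limited. They are supplementary and lie outside the article's definitions of both perceived quality (HVOK) and patient-reported outcome (SF-12 with OHS or OSS).

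**Conclusion.** The point holds in two limited parts.

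1. Followed as printed, the schedule collects meaningless answers to RCS items 2 and 3 from hip patients before surgery, and to item 3 from shoulder patients at both follow-ups: 4 of 15 item-by-visit combinations. This assumes that the forms carry all three items in the printed wording, which the article implies but does not show.
2. Discharge HVOK, one of three HVOK occasions, is promised for multiple linear regression and assigned to neither named model.

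The impact is moderate. Because RCS is listed among the secondary outcomes whose correlation with CMD-SQ is called the main result, ill-fitting answers could reach reported analyses. The test of the hypothesis does not depend on them, and HVOK at 12 and 52 weeks is unaffected.

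**What to change.** - **RCS before surgery:** limit it to item 1, or drop RCS from the hip preoperative form. State that items 2 and 3 are not used as baseline values.
- **RCS item 3 at 12 and 52 weeks:** print a shoulder version that puts the operated shoulder in place of the hip, and analyse this item separately by joint.
- **Discharge HVOK:** add a third regression to Statistical analysis, with discharge HVOK as outcome, preoperative CMD-SQ as predictor, and the same covariates as the other two models (the Charlson Index and the sociodemographic variables).
- **Abstract:** align the questionnaire schedule with Design.

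The cost is one reworded item, a shorter preoperative form, one more analysis and a wording correction, with no extra patients or visits. There are two downsides: the adapted item departs from the RCS item as its developers published it, so shoulder results on it are not directly comparable with the hip version, and the added regression is one more result to report.
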